### Participant timeline

The data collection procedure will include enrolment, interventions after baseline (pre-intervention) and assessments at pre-intervention and 6 months post intervention (see Additional file 2: Standard Protocol Items: Recommendations for Interventional Trials (SPIRIT) Checklist, the SPIRIT Figure (Fig. 1) and Additional file 1: Figures S2, S3 and Table S1).

**Fig. 1 Fig1:**
[figure not shown]
Timeline for trial activities, interventions and assessments

### Enrolment

Following ethical approval and permission being obtained, schools will be contacted to be recruited to participate. Once all schools agree to participate, randomisation will occur.

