## Methods

### Trial design

This study will make use of a stratified cluster randomised controlled trial with the schools as the unit of randomisation. Using a 1:1 allocation ratio, schools will be stratified into two quintile groups (lower versus higher). The quintiles will be randomised, to receive the CCR intervention or usual practice, to eliminate selection bias and to control for any extraneous variables. This will also allow each lower and higher quintile school an equal opportunity to be included (See Additional file 1: Figure S2).

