### Recruitment

To achieve adequate enrolment of participants, school recruitment will be conducted which is scheduled to commence on 19 January 2017. Thereafter, the returned consent and assent forms will determine whether the target sample size was achieved. If it has, then no more schools will be recruited.

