### Assignment of interventions

#### Allocation: sequence generation, allocation concealment mechanism and implementation

The statistician will generate the computerised allocation sequence. The random allocation ratio will be 1:1 while the randomisation will be stratified into 2:1 where the lower quintile has a higher number of assignments of participants per school when compared to the higher-quintile schools. The written allocation of the assignment of participants will be sealed in an envelope which contains identification numbers. These identification numbers will be distributed across the lower- and higher-quintile schools. A sufficient number of schools will be included to meet the targeted sample size. The researcher will open the envelope to determine the allocation of schools. The stratification of the sample will occur in the following order; mixed-gender schools, schools within quintiles 2 and 3 and 4 and 5 and finally according to the eligibility characteristics and restrictions.

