### Blinding

The principal investigator will be fully blinded to the study. The primary researcher will complete the following: obtain permission from the relevant individuals; recruit participants; recruit research assistants; assist research assistants with training of intervention group teachers to use CCR intervention and; observe the administration of the CCR intervention only along with research assistants. A team of research assistants will be utilised to assist with randomisation and blinding of the primary researcher regarding the administration and data capturing of the SROM.

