## Discussion

### Harms

The teacher will be consulted prior to data collection to identify whether there is a CWS in the classroom. The CWS may choose to not participate or to not have the intervention run in their classroom. Teachers will also be asked to note any concerns. Any participants requiring counselling will be referred to a psychologist by the researcher. However, in all the previous studies, no concerns or need for counselling have been identified or required [18, 19]. In fact, the studies showed minimal improvements in the ratings of attitudes at 1 month post intervention while more prominent results were observed at 6 months post intervention [18, 19]. Other benefits include access and training to the CCR intervention for all schools and teachers. The benefits, therefore, outweigh any potential risks that may be experienced. The data will be collected at schools where participants are comfortable, and the use of logbooks will be vital in informing if any harms are noted.

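### The protocol does not keep school allocation hidden until students have consented and completed the baseline SROM, and the stated blinding of the person who recruits them does not cover recruitment

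*Protocol article*

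**What the plan says.** All references are to the protocol article.

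- **Enrolment:** "Once all schools agree to participate, randomisation will occur". No student-level step is named as a precondition.
- **Recruitment:** after school recruitment is described, "Thereafter, the returned consent and assent forms will determine whether the target sample size was achieved". The next sentence reads "If it has, then no more schools will be recruited", so the number of schools depends on the student consent count.
- **Allocation:** the statistician generates the sequence and it is kept in a sealed envelope. Then "The researcher will open the envelope to determine the allocation of schools".
- **Blinding:** "The primary researcher will complete the following: obtain permission from the relevant individuals; recruit participants; recruit research assistants". The same role helps train the CCR teachers and observes delivery. The blinding described for it concerns only how the SROM is given and captured.
- **Harms:** teachers are asked before data collection whether a child who stutters is in the class, and "The CWS may choose to not participate or to not have the intervention run in their classroom".
- **Trial design:** schools are the unit of randomisation, and randomisation is intended "to eliminate selection bias and to control for any extraneous variables".
- **Statistical methods:** the student is the unit of analysis.

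**The concern.** In a cluster trial, randomising schools makes the schools comparable. It makes the students comparable only if their entry does not depend on the arm. Here students enter through parental consent and their own assent, and they are the units analysed. If the recruiter, the teacher or the family knows the arm when consent is sought, the consenting students in the CCR schools can differ from those in the control schools.

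The outcome makes this more than a formality. Attitude to stuttering is what the SROM measures, and it is also a plausible reason to agree or decline to take part in a study about stuttering. Intention-to-treat analysis and GEE work on the students who enrolled. Neither restores a balance lost at entry.

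**Working it through.** The protocol gives no figure to reproduce on this point. The check sets the sections side by side.

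**1. Which orders fit the text?**

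- *Order A:* schools agree, allocation is revealed, consent is collected and counted, and schools are added if the count falls short. This follows Enrolment literally. If there is a shortfall, it clashes with Recruitment, because not all schools had agreed when randomisation took place.
- *Order B:* schools agree, consent is collected and counted, schools are added if needed, and then all are randomised. This is consistent with both sections, but neither states it. Enrolment names school agreement alone as the trigger.

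In the Recruitment sentence, 'Thereafter' refers back to school recruitment, not to randomisation. The text therefore permits both orders and excludes neither.

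**2. Is the baseline SROM protected?** Participant timeline puts the intervention after baseline. That is not the same as revealing allocation after baseline. The Interventions section has CCR teachers review the material, attend training and then take a further two weeks before delivery. A baseline taken before delivery could thus still fall after teachers know their arm. Likewise, the Harms section places the question about a child who stutters before data collection, which need not mean before allocation.

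**3. Who knows the arm, and who recruits?**

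- The primary researcher recruits participants (Blinding).
- The same role learns the arm at the latest when helping to train CCR teachers (Blinding). This matters if consent is still open at that time.
- The envelope is opened by 'the researcher' (Allocation). This appears to be the same role: the Intervention section has the researcher observe delivery, Blinding gives that task to the primary researcher, and Dissemination policy uses both terms for one role. It remains an inference.
- The fully blinded principal investigator is not the role listed as recruiting. Research assistants help with randomisation, but nothing says that they keep the allocation from the recruiter.

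**4. What would the analysis remove?** Suppose a fraction *f* declines in one arm only, and those who decline differ from those who stay by *g* points. The arm mean then shifts by *f* × *g*. The sample size section specifies adjustment for baseline SROM. With a baseline slope *b*, a lasting attitude gap leaves about *f* × *g* × (1 − *b*). Selection on readiness to respond to the CCR, beyond what the baseline score shows, is not reduced by this term. The document gives none of *f*, *g* or *b* at six months, so no number follows. The test-retest value of 0.84 in the outcome section is a reliability figure and is not given as a six-month slope.

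**The case against.** The strongest reply is that the order is unclear, not wrong. Read together, Enrolment and Recruitment allow consent first and randomisation last, and on that reading there is no contradiction. The article is condensed, and the timeline figure and additional files, which are not shown, may settle the matter. This stands as far as it goes: the document does not establish that consent follows allocation. It does not dispose of the point, because the only trigger actually written is school agreement, and the blinding written for the recruiter leaves recruitment out.

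A second reply is that no section says families are told their arm when they consent. Participants in both arms see the stuttering video, and all participating schools are promised the CCR. That weakens the presumption of a large effect but does not close the route through an informed recruiter or teacher.

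Two stronger readings are tempting. A reader might infer that the person who opens the envelope also counts the forms; the Recruitment section names nobody. A reader might also treat the option of a child who stutters to stop the CCR in a class as selection into an arm. It is better seen as non-delivery: it dilutes the effect, and the stated intention-to-treat principle already keeps that class in its randomised arm.

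**Conclusion.** The point holds as a gap in protection, not as a demonstrated bias. As written, the plan lets student consent, assent and baseline measurement take place with the school's arm known, and nothing stated shields the recruiter from it. The aim of eliminating selection bias is therefore not secured, and Enrolment and Recruitment need to be reconciled.

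A reader might go further and say that the plan reintroduces selection bias, or attach a share of the planned 5.25-point difference to it. The documents support neither. Order B is possible, the refusal rates and score differences needed for a figure are absent, and baseline adjustment would absorb part of a baseline attitude gap. What adjustment would not absorb is selection on receptiveness to the CCR.

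The conclusion assumes that the missing timeline figure does not already place consent and baseline before allocation. The apparent identity of the two researcher roles strengthens it, but it does not depend on that. The correction is worthwhile because it is cheap and protects the primary comparison.

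**What to change.** In Enrolment and Recruitment, state one sequence:

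1. The school list is final, including any schools added after the consent count.
2. Parental consent and student assent are complete.
3. The teacher has reported any child who stutters, and that child's choice is recorded.
4. The baseline SROM is complete.
5. Only then is allocation revealed, for all schools in one batch.

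Trial status says that recruitment began on 31 January 2017. If schools have already been allocated, state the order that was actually followed and report consent rates by arm.

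The change reorders steps already planned and adds no visits. Its cost is that allocation is revealed somewhat later, which delays teacher training.

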### Interventions

All participants will view a video of a CWS and stuttering will be defined in order to ensure that all participants are provided with a uniform definition of a CWS in terms of how it looks and sounds. A 1-h training session (administration guidelines, purpose and aims, discussion ideas, addressing questions) will be held with the teachers in the intervention groups only, once they reviewed the CCR intervention. Teachers will be given a 2-week period to review the CCR intervention again before they administer it. Control groups will not receive the CCR intervention during this phase.

### Assessments

The SROM will be administered at pre-intervention and again at 6 months post intervention. The limitation of using the SROM repeatedly over the 6-month period is acknowledged. In the absence of an equivalent validated measure, the SROM will be used as there will be a time lapse between administrations reducing potential re-intervention bias. Once the data is collected, teachers from the control groups will be provided with the CCR intervention and will be offered training.

### Sample size with power analysis

The sample size calculation was based on previous CCR intervention studies [18, 19, 26]. With the proposed sample size of *n* = 350 students (*k* = 10 schools) in each of the two groups (i.e. assuming a 1:1 allocation ratio), the study will have the power of 80% to yield a statistically significant result using a generalised estimating equations (GEE) model (assuming an intention-to-treat (ITT) principle for the analysis) of the difference between mean in SROM global scores at 6-month adjusting for baseline (pre-intervention) SROM global score at alpha = 0.05. This computation is based on a pilot study [19] which assumes that SROM global scores are normally distributed, the mean difference is 5.25 (corresponding to mean of 77.91 (for the intervention group) versus 72.66 (for the control group)) and the common within-group standard deviation is 11.90 and an ICC (intra-school correlation coefficient) of 72.70.

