This led to the development of the South African specific intervention, the CCR intervention. It was developed and has been refined since 2009 as part of a series of the University of Cape Town (UCT) projects. The CCR intervention yielded positive results at 1 month post-intervention within the lower and higher quintile population respectively [18, 26] and more so at 6 months’ post-intervention [19]. The feasibility of a future Randomised Controlled Trial (RCT) study additionally reported potential effectiveness of the CCR intervention at 1 and 6 months’ post-intervention as well as procedural aspects [19]. The findings were however inconclusive as it called for a more rigorous design method [19]. It was also reported that a RCT was feasible despite concerns regarding the retention of participants as stringent methods could be put in place [19]. A RCT was thus recommended as the next stage in these projects [19].

The CCR intervention addresses pro-social behaviours and skills, including but not limited to the promotion of positive behaviour change, peer support and resilience through intervention [16] in the areas of Positive Social Distance (PSD), Verbal Interaction (VI) and Social Pressure (SP) in the CCR intervention and Stuttering Resource Outcomes Measure (SROM). The areas of PSD, VI and SP are additionally measured using the SROM. PSD represents the overall ease, acceptance of and comfort a child feels when around CWS [14, 15] e.g. ‘I would let a child who stutters hang out with us’. VI evaluates peer’s negative thoughts, emotions and feelings, e.g. frustration experienced towards a CWS [14, 15]. SP evaluates general thoughts regarding CWS through examining social pressure and subjective norms [13]. An example is ‘I would be ashamed to be seen with a child who stutters’. The promotion of these pro-social behaviours and skills may facilitate the prevention of anxiety and depression [16] especially as CWS are placed at a high-risk of being teased and bullied due to their stutter [1–4].

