#### Nested studies

A few challenges were highlighted in the previous study such as poor retention of participants [19]. It is unknown what other challenges may arise. It is for this reason that the researcher, research assistants and teachers will be required to have logbooks in which detailed accounts and experiences are documented.

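### The 80% power is stated for 350 students per arm with no allowance for loss shown, and that target is judged at consent, although the pilot behind the calculation had poor retention

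*Protocol article*

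**What the plan says.** All references are to the protocol article.

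- **Sample size with power analysis** proposes "350 students (*k* = 10 schools) in each of the two groups", "assuming a 1:1 allocation ratio", and says that with this sample "the study will have the power of 80% to yield a statistically significant result using a generalised estimating equations (GEE) model". The comparison is of mean SROM global scores at 6 months, "adjusting for baseline (pre-intervention) SROM global score at alpha = 0.05". The inputs are attributed to a pilot study. No loss rate or inflation factor appears.
- **Recruitment** says how the target is checked: "Thereafter, the returned consent and assent forms will determine whether the target sample size was achieved". If it was, no further schools are recruited.
- **Nested studies** says: "A few challenges were highlighted in the previous study such as poor retention of participants". The study cited there is the same one that the sample size section cites as its pilot.
- **Background, Stuttering intervention** reports that a randomised trial was judged feasible "despite concerns regarding the retention of participants as stringent methods could be put in place".
- **Data collection** plans to support retention by scheduling visits to suit the schools. **Data management** plans imputation and gives absenteeism as an example of a cause of missing data.

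**The concern.** One figure, 350 per arm, does two jobs. In the sample size section it is the number to which 80% power for a 6-month comparison is attached. In the Recruitment section it is a count of consent and assent forms, taken before a follow-up of 6 months. The two agree only if every consented pupil in every school provides a 6-month SROM, and the protocol's own account of the pilot gives reason to doubt that.

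The means and SD were taken from the pilot, but its retention is not seen to be used. Convenient scheduling may reduce loss but puts no number on it. Imputation does not in general restore the information in scores that were never observed. If loss occurs and the 80% was exact, a null result would be read against a somewhat higher power than the trial had.

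**Working it through.** **Inputs from the sample size section.** k = 10 schools per arm; 350 students per arm, so m = 350/10 = 35 per school; difference 77.91 - 72.66 = 5.25; SD 11.90; alpha 0.05 (two-sided assumed, as the section does not say); ICC printed as 72.70. No retention rate is given anywhere, so loss is shown as a range.

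**Formula.** SE = sqrt(2 x 11.90^2 x [1 + (m - 1) x ICC] / (k x m)). Power comes from 5.25/SE, by the normal approximation (z) or the noncentral t on 2k - 2 degrees of freedom (18 when k = 10).

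**Step 1: can the stated 80% be reproduced?** No.
- With no clustering, SE = sqrt(2 x 141.61/350) = 0.90 and power exceeds 99.9%; 81 students per arm would suffice for 80%.
- An ICC cannot be 72.70. Read as 0.727, the design effect is 1 + 34 x 0.727 = 25.7, SE = 4.56 and power is 20.9% (z) or 19.2% (t).

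**Step 2: a working starting point (assumption).** Solving for the ICC that gives exactly 80% at k = 10, m = 35, without baseline adjustment:
- z: ICC 0.098, design effect 4.34, SE 1.874, 5.25/1.874 = 2.80.
- t: ICC 0.085, design effect 3.88, SE 1.772, 5.25/1.772 = 2.96.

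**Step 3: apply loss from that point.**

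| Scenario per arm | m | k | Power, z | Power, t |
|---|---|---|---|---|
| No loss | 35 | 10 | 80.0% | 80.0% |
| 10% of pupils | 31.5 | 10 | 79.1% | 79.0% |
| 20% of pupils | 28 | 10 | 78.0% | 77.7% |
| 30% of pupils | 24.5 | 10 | 76.6% | 76.1% |
| 40% of pupils | 21 | 10 | 74.7% | 74.0% |
| One whole school | 35 | 9 | 75.7% | 75.1% |

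Example (z, 20% loss): design effect 1 + 27 x 0.0982 = 3.65; SE = sqrt(2 x 141.61 x 3.65/280) = 1.922; 5.25/1.922 = 2.73; power 78.0%. Pupil loss costs little because losing pupils also lowers the design effect. Losing a school does not.

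**Step 4: how far this depends on the starting point.**
- *Baseline adjustment.* With a baseline correlation of 0.5 (assumption), residual variance scaled by 1 - 0.25 and the ICC re-solved to give 80% (0.141, z), 20% loss gives 78.6%. The cost is smaller still.
- *ICC 0.727.* Power goes from 20.9% to 20.8% at 30% pupil loss, so attrition is immaterial.
- *ICC 0.05 (assumption, z).* Power is 94% with no loss, 93% at 20% pupil loss, and 86% with 8 schools per arm and 20% pupil loss. It stays above 80% throughout.

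**The case against.** The strongest reply has four parts.

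1. **The article never says that loss was ignored.** A reader might infer that the 80% was computed with none. The text does not establish this: the figure cannot be reproduced from the printed inputs, and a condensed article may omit an allowance made elsewhere. This stands. What the article does show is that one number serves as both the powered sample and the consent target, with no allowance visible between them.

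2. **The effect is small.** A reader might conclude that the trial will fall short of its stated power, whatever the ICC. The documents do not support that. From the working starting point, 20% to 30% pupil loss costs about 2 to 4 points; at an ICC of 0.05 power stays above 80% in the scenarios checked, and at 0.727 attrition makes almost no difference. This also stands.

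3. **Whole-school loss is not in evidence.** The article speaks of retention of participants and of absenteeism, not of schools withdrawing. The 75-76% figure is therefore a what-if.

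4. **The plan has safeguards.** Scheduling and imputation are planned, and the allocation section promises enough schools to meet the target sample size. But that target is still the consent count, and none of these measures states how many 6-month scores are expected. This part of the reply does not remove the point.

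**Conclusion.** The point holds as a modest reporting correction. The protocol states 80% power for 350 students in 10 schools per arm, shows no allowance for loss, judges that target at consent, and reports poor retention in the pilot that supplied its inputs. As written, the power figure is tied to complete follow-up.

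The likely cost is a few points. The range of about 78% down to 74% for 20% to 40% pupil loss rests on three assumptions: that 80% was exact at 350 analysed per arm, that the ICC was therefore about 0.085 to 0.098, and that no credit is taken for baseline adjustment. None of these can be confirmed from the article.

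The point is secondary to the impossible ICC of 72.70. Until that is corrected, neither the 80% nor any loss from it can be verified.

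**What to change.** Leave enrolment unchanged.

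1. Correct the ICC first; the restatement below depends on it.
2. In *Sample size with power analysis*, state the power for the number of pupils and schools expected to have a 6-month SROM, using the pilot's observed retention rate. A short table would do: 0, 20, 30 and 40% pupil loss, by 10, 9 and 8 schools per arm.
3. In *Recruitment*, say that 350 per arm is an enrolment figure and not the analysed number.

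The cost is two sentences and a small table. The retention rate should be available from the pilot's records. The stated power may become a few points less favourable.

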#### Statistical methods

The analysis will follow the intention-to-treat (ITT) principle and will be reported according to CONSORT guidelines [32]. The GEE will be used to compare the groups on global SROM and subscales to address the primary objective. Assuming an exchangeable correlation structure within a school, GEE will allow for possible clustering within a school to be accounted for. The unit of analysis will be the grade-7 student. The results will be reported as estimate of the difference between groups, 95% confidence interval and associated *p* value. All *p* values will be reported to three decimal places with those less than 0.001 reported as *p* < 0.001. The criterion for statistical significance will be set at alpha = 0.05. The subgroup hypothesis will be tested by adding an interaction term of the quintile group (lower versus higher) × intervention (CCR versus usual practice) in the model. Similarly, this analysis will be used to address the secondary objective by analysing the PSD, VI and SP constructs on the SROM. The subgroup analysis will use this method of analysis to address the subgroup analysis between and across the quintiles. See Additional file 1: Table S1 for a summary table of the objectives, outcomes, hypotheses and methods of analysis.

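### The 80% power claim rests on an intra-school correlation of 72.70, an impossible value, so the stated power does not follow from the stated inputs

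*Protocol article*

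**What the plan says.** The section on sample size with power analysis in the protocol article proposes 350 students in 10 schools in each of two arms, allocated 1:1. On that basis it says "the study will have the power of 80% to yield a statistically significant result". The analysis is a GEE model of the 6-month SROM global score, "adjusting for baseline (pre-intervention) SROM global score at alpha = 0.05".

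The inputs are attributed to a pilot study. The section states that "the mean difference is 5.25" (77.91 against 72.66), and adds "the common within-group standard deviation is 11.90 and an ICC (intra-school correlation coefficient) of 72.70". There is no percent sign. The section does not give a design effect, a correlation between baseline and 6-month scores, or the sidedness of the test.

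No other section supplies a usable ICC. The section on subgroup analyses says only that schools behaved as clusters in the feasibility study. The statistical methods section specifies an exchangeable correlation within school.

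**The concern.** The article itself expands ICC as a correlation coefficient, and a correlation of 72.70 does not exist. In a trial that randomises schools, the ICC largely decides what 350 students per arm are worth. With 35 students per school, each 0.01 of ICC adds 34 × 0.01 = 0.34 to the design effect.

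An article may leave detail to a fuller document, but this one chose to state the calculation, and one of its governing inputs is wrong as printed. The plausible repairs lead to very different trials. Under some, a null result would say little about whether the intervention works. Under another, the size is adequate. A reader cannot tell which trial is being run.

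**Working it through.** **Inputs from the sample size section.** Difference Δ = 77.91 − 72.66 = 5.25; SD = 11.90, so variance = 141.61; k = 10 schools and 350 students per arm, so m = 35 per school on average; alpha = 0.05; claimed power 80%.

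**Assumptions.** The test is two-sided (the article does not say). The SD is the total SD within an arm. Schools are of equal size. Baseline adjustment with correlation r multiplies the variance by 1 − r². The article gives no r for the power calculation. I use r = 0 and r = 0.84, the latter being the SROM test-retest reliability reported under primary outcomes, which is optimistic for a 6-month gap.

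**Formulas.** Design effect DE = 1 + 34 × ICC. Effective n per arm = 350 / DE. SE = 11.90 × √(2 / effective n). Normal power = Φ(Δ/SE − 1.96). The t version uses the noncentral t with 2 × (10 − 1) = 18 df.

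**Which ICC would give 80%?** Without clustering, n per arm = 2 × (1.960 + 0.842)² × 141.61 / 5.25² = 80.65. The design therefore affords DE = 350 / 80.65 = 4.34, so ICC = 3.34 / 34 = 0.098. On the t basis the figure is 0.085. Neither value appears in the article.

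**Reading 1: a percentage, ICC = 0.727.** DE = 1 + 34 × 0.727 = 25.7; effective n = 13.6; SE = 4.56; Δ/SE = 1.15. Power is 21% (normal) or 19% (t). With r = 0.84, the SE falls to 4.56 × √0.2944 = 2.48, and power is 56% or 52%. Reaching 80% would need r of about 0.91 (normal) or 0.92 (t). The difference detectable with 80% power at r = 0 is (1.960 + 0.842) × 4.56 ≈ 12.8 points, against the 5.25 planned.

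**Reading 2: a between-school variance of 72.70.**
- Out of a total of 141.61: ICC = 72.70 / 141.61 = 0.513; DE = 18.5; effective n = 19.0; SE = 3.86.
- Added to a within-school variance of 141.61: SE = √(2 × (72.70/10 + 141.61/350)) = 3.92.

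**Reading 3: a decimal slip, ICC = 0.0727.** DE = 3.47; effective n = 101; SE = 1.68; Δ/SE = 3.13. Power is 88% or 84% before any baseline gain.

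| Reading of 72.70 | Power, r = 0 (normal / t) | Power, r = 0.84 (normal / t) |
|---|---|---|
| 0.727 | 21% / 19% | 56% / 52% |
| Between-school variance, total 141.61 | 27% / 25% | 71% / 66% |
| Between-school variance, added to 141.61 | 27% / 24% | 69% / 65% |
| 0.0727 | 88% / 84% | above 99% / above 99% |

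**The case against.** The strongest reply is that 72.70 is a misprint for 0.0727 and that the design is sound. This has some force. On the t basis at 0.0727, 9 schools of 35 per arm give 79.7% and 10 give 84.2%, so 10 schools is the smallest whole-school design that reaches 80%. Taking 11.90 as the SD within schools gives 81.4%. On the normal basis 8 schools, or 280 students, give 80.0%, and 280 / 0.8 = 350 if a 20% loss was allowed for, although the article states no such allowance. A reader might infer that no sensible reading of 72.70 yields the claimed power; these figures show that this goes too far. What does not stand is treating 0.0727 as established. It needs a thousand-fold shift of the printed number, and nothing in the text points to it.

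A second reply is that the model adjusts for baseline, so figures without that gain understate power. That is fair, and the correlation is unstated. Even so, 0.84 does not bring the percentage or variance readings to 80%.

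A third is that 72.70 may simply be the wrong number, since it lies close to the control mean of 72.66 in the same sentence. That is conjecture. If it is true, none of the tabulated readings applies and the ICC is still unknown.

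A reader might also infer that 350 ignores attrition, because the nested studies section reports "poor retention of participants" in the earlier study. The article does not say whether 350 is before or after loss, and the effect is small: with the ICC at 0.098, losing 20% of students moves power only from 80% to 78%. I do not press that point.

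**Conclusion.** The point holds: the printed ICC is impossible, and the 80% power does not follow from the inputs as stated. At r = 0, power is about 20% if 72.70 is a percentage, about a quarter if it is a between-school variance, and 84% to 88% if it is 0.0727. With r = 0.84 the first two rise to 52–56% and 65–71%, still below target.

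These figures assume a two-sided test, equal school sizes and a total SD of 11.90. A reader might infer from the low figures that the trial is underpowered. The article does not support that conclusion, because the true ICC is not in it. What is established is that the claim cannot be verified, and that the most literal repair contradicts it.

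**What to change.** Replace 72.70 with the ICC from the pilot data, on the 0 to 1 scale. State the baseline-to-6-month correlation assumed, or say that none was. Recompute with a design effect of 1 + 34 × ICC, and restate the power that 10 schools of 35 per arm delivers for a difference of 5.25. If the ICC really is about 0.7, withdraw the 80% claim and give the power, or the smallest detectable difference, that the design supports.

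The cost is a rewritten paragraph and one calculation from data the sponsor should already hold. No extra schools or students are needed to correct the statement. The downside is that the restated power may be less favourable.
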